### Measures

All questions asked at baseline and subsequent follow-ups can be found in Multimedia Appendix 3.

For hypotheses 1, 6, and 7:

Primary outcome measures: Total weekly alcohol consumption and frequency of heavy episodic drinking.Secondary outcome measures: Classification as risky drinker according to Swedish guidelines.

For hypothesis 2:

Mediation measures: Confidence in one’s ability to reduce consumption, importance of reducing, and knowledge of how to reduce consumption.

For hypotheses 3 and 4:

Primary outcome measures: Enrollment rates from each study conditionSecondary outcome measures: Recall of trial procedures measured through a series of questions.

For hypothesis 5:

Primary outcome measures: Rates of additional information being requested by pressing on the supplied hyperlink.

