**Main Hypotheses**
1. Alcohol consumption will differ between intervention and control groups, with the intervention group drinking less than control at 2 and 4 months after randomization. The 2-month interval will be primary.2. Confidence, importance, and know-how at 1-month follow-up will mediate the effects of the intervention on drinking outcomes at 2-month follow-up. The same measures at 2-month follow-up will mediate the effect on drinking outcomes at 4-month follow-up.3. Enrollment rates will differ between groups Consent-1 and Consent-2.4. Accurate recall of study parameters will differ between groups Consent-1 and Consent-2.5. Rates of accessing further information will differ between groups Info-1 and Info-2.

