### Statistical Analysis Methods

All analyses will be done under the intention-to-treat principle, where all randomized individuals will be included. Missing outcome data will initially be handled by a complete-case analysis, which assumes that data are missing at random (MAR). If data are systematically missing, then it may be the case that early responders differ from late responders and, in extension, that late responders are more similar to nonresponders. We will, therefore, explore the plausibility of the MAR assumption by regressing the primary outcomes on the number of follow-up attempts needed before a response was recorded. To further explore the MAR assumption, attrition will be investigated among study groups by comparing baseline characteristics between those who did and did not respond at follow-up. A sensitivity analysis that includes imputed values for missing outcome data (using multiple imputation by chained equations [58]) will also be performed. Data will be graphically examined for outliers or data input errors, and sensitivity analyses will be performed excluding any erroneous data points.

For all models, coefficients of interest will be assessed for statistical significance using a null hypothesis testing approach, where tests will be 2-tailed at the .05 significance level. Alongside the null hypothesis tests, posterior distributions using a Bayesian approach will be calculated for each coefficient. Both significance tests and posterior distributions will create a basis for scientific inference [59].

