#### Baseline

Baseline characteristics will be compared among the different groups using chi-square tests or Fisher exact tests for comparison of proportions and Mann-Whitney *U* tests for comparison of means.

#### Hypotheses 1, 6, and 7

Total weekly alcohol consumption and frequency of heavy episodic drinking are likely to be skewed and overdispersed, and we will, therefore, analyze both using negative binomial regression. Classification as a risky drinker will be analyzed using logistic regression. Both unadjusted and adjusted regression models will be created. Adjusted models will include baseline values of the respective outcome measures and responses to the baseline questions regarding sex, civil status, age, motivation, importance, and know-how. As alcohol consumption differs significantly among age groups, and possibly also the effect of the intervention, multilevel models will also be created in which slopes are allowed to vary among age groups. Effect modification tests will be performed in all models to assess if any of the baseline characteristics moderate the effect of the intervention. The adjusted models will be the primary models.

#### Hypothesis 2

Mediators will be explored using a causal inference framework [60], where Monte Carlo methods are relied upon for inference. This allows for any type of model (linear and nonlinear) to be used to represent the relationships between the group allocation, mediating variable, and outcome. A total of 4 models will be created for each outcome measure, 3 that investigate the mediating factors on their own and a fourth that incorporates all mediators at once. If any baseline characteristics were found to moderate the effect in the primary analysis, then additional mediator models will be created to include these as moderators.

#### Hypotheses 3 and 4

Whether or not individuals decided to give informed consent will be regressed against group allocation (Consent-1 and Consent-2) using logistic regression. Adjusted regression models will be explored that include baseline characteristics (including only participants who gave informed consent). Differences among the 2 groups on responses to the recall questionnaire will be investigated using chi-square tests or Fisher exact tests for comparison of proportions.

#### Hypothesis 5

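### Mediation is ranked as a main hypothesis but spread over about 24 indirect effects under a general .05 rule, with none named as decisive and the analysis text calling it exploration

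*Protocol article*

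**What the plan says.** The list of main hypotheses in the protocol article includes, as item 2, "Confidence, importance, and know-how at 1-month follow-up will mediate the effects of the intervention on drinking outcomes at 2-month follow-up". It continues: "The same measures at 2-month follow-up will mediate the effect on drinking outcomes at 4-month follow-up". Hypotheses 6 and 7 are on a separate exploratory list; mediation is not.

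The Measures section gives three mediators: "Mediation measures: Confidence in one’s ability to reduce consumption, importance of reducing, and knowledge of how to reduce consumption". For hypotheses 1, 6 and 7 it gives two primary outcomes, "Primary outcome measures: Total weekly alcohol consumption and frequency of heavy episodic drinking", and one further outcome, "Secondary outcome measures: Classification as risky drinker according to Swedish guidelines". Hypothesis 2 refers only to drinking outcomes in general.

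Under Statistical Analysis Methods, the Hypothesis 2 subsection says that mediators will be explored in a causal inference framework with Monte Carlo inference. It fixes the model set: "A total of 4 models will be created for each outcome measure, 3 that investigate the mediating factors on their own and a fourth" containing all three mediators. If moderators emerge in the primary analysis, "then additional mediator models will be created to include these as moderators".

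The opening of Statistical Analysis Methods sets the testing rule: "For all models, coefficients of interest will be assessed for statistical significance using a null hypothesis testing approach", two-sided at .05. Bayesian posterior distributions are reported alongside, and both are to inform the conclusions.

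Hypotheses 1, 6 and 7 each make the 2-month interval primary. Hypothesis 2 has no such sentence, although the Abstract calls the 2-month follow-up primary in general terms.

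**The concern.** A main hypothesis should carry a rule for when it counts as supported. Here the article does not say whether all three factors must mediate, whether one is enough, or whether the joint model decides. It does not say on which outcome or over which interval. With a general .05 rule, a report could present whichever indirect effect crossed the threshold as support for a main hypothesis.

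At stake is the second key objective in the Aims, on how far the effect runs through these psychosocial factors. A reader could be told that, say, know-how is the active ingredient when that result is one chance finding among many. The estimate of the intervention's effect on drinking (hypothesis 1) is not touched.

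**Working it through.** **1. The plan's own figure.** The article gives no error rate for hypothesis 2. Its stated figures are an average power of 0.79 at N = 1800 and an expected loss to follow-up of 326 (interquartile range 231 to 398). A Monte Carlo run with the inputs in Power Calculation gave 0.794 and 325 (231 to 398). Both reproduce, and N = 1800 (about 900 per arm) is used below.

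**2. Counting the indirect effects.**
- Per outcome and interval: 3 from the single-mediator models + 3 from the joint model = 6.
- Two primary outcomes and two intervals: 6 × 2 × 2 = 24. These are 3 × 2 × 2 = 12 distinct paths, each estimated twice.
- If the joint model gives one combined effect: (3 + 1) × 2 × 2 = 16.
- With risky drinking as a third outcome: 6 × 3 × 2 = 36.
- Data-dependent moderated models come on top and are not counted.

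**3. Independent-test benchmark.** 1 − 0.95^k gives 46% for k = 12, 56% for k = 16 and 71% for k = 24. These are not the answer, for two reasons: the effects are correlated, and an indirect effect needs both of its paths to be real (a: intervention to mediator; b: mediator to drinking).

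**4. Error rate of one indirect effect.** If an effect is declared when both paths are significant at .05, its false rate is P(a significant) × P(b significant). With 900 per arm, the standard error of a standardised mediator difference is √(2/900) = 0.0471.
- All mediators moved by 0.3 SD, b = 0: z = 0.3/0.0471 = 6.4, so power for a is about 1 and the rate is about 1 × .05 = .05.
- Moved by 0.1 SD, b = 0: z = 2.12, power = Φ(2.12 − 1.96) ≈ 0.56, and the rate is about 0.56 × .05 = .028.
- a = 0, b real: about .05. Only 3 mediators × 2 time points = 6 distinct a-tests exist, so the independent benchmark is 1 − 0.95^6 = 26%.
- Both zero: .05 × .05 = .0025.

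The simulated per-effect rates agree: about .05, .027 to .030, about .05, and .002 to .003.

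**5. Simulated chance of at least one false indirect effect among the 24.** Assumptions not in the article: linear models; correlations of 0.2-0.8 between mediators, 0.4-0.9 between outcomes and 0.4-0.9 over time; mediator shifts as shown. The columns run from the lowest to the highest correlation set.

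| Truth | Low | Mid | High | Very high |
|---|---|---|---|---|
| All 3 mediators moved 0.3 SD, none affects drinking | 51% | 49% | 45% | 36% |
| All 3 moved 0.1 SD, none affects drinking | 31% | 32% | 30% | 24% |
| One moved 0.3 SD, none affects drinking | 24% | 23% | 21% | 19% |
| None moved, all predict drinking | 25% | 24% | 17% | 13% |
| Neither path exists | 4% | 4% | 3% | 2% |

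Replacing the both-paths rule with Monte Carlo intervals for the product of the two paths (mid correlations) gave 49% for the first row and 27% against 24% for the fourth. A second simulation at N = 1800, again with assumed correlations, gave 46-52%, about 31%, 18-24% and about 3% for rows 1, 2, 4 and 5.

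**6. Narrower families.** If only the 2-month interval counts (12 effects), the first row becomes 26-30%. With one outcome as well (6 effects), it is 17-19%. With one named effect it is at most 5%. Bonferroni over 24 would test each at 0.05/24 = 0.0021.

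**The case against.** The best defence is that the article treats mediation as estimation. The Aims ask to what degree the effect is mediated, the Mediation section again speaks of estimating, and the analysis section speaks of exploring. This stands in part. It shows that an exploratory reading was probably meant, but it contradicts the main-hypothesis label, and the article does have a separate exploratory list. The Limitations section calls only the substudies preliminary, and mediation is not one of the three.

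Second, nothing in the text says that one significant effect is enough. Hypothesis 2 names all three factors; if all had to mediate, multiple testing would not inflate the error. This is correct. A reader might infer an any-one-suffices rule, but the article neither states nor excludes it, so every percentage here is conditional on that reading.

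Third, the .05 rule refers to coefficients, whereas an indirect effect is a derived quantity with Monte Carlo inference, and posteriors are reported as well. Applying the rule to every indirect effect is natural but not explicit. The posteriors do not replace the tests, which remain a stated basis for inference.

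Fourth, multiplicity is often left to a statistical analysis plan, and none is shown. The absence of an adjustment would therefore not be a finding in itself. The point rests on what the article does fix: the main label, the model set and a .05 rule for all models.

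**Conclusion.** The point holds as a cheap improvement. A main hypothesis covers about 24 indirect effects on the primary outcomes (16 on the narrowest count), under a general .05 rule, with none marked as decisive and with analysis wording that conflicts with its rank.

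If any one significant effect counts as support, the chance of at least one false mediation finding is roughly 25-50% when the intervention moves all three mediators and none affects drinking. It is roughly 13-25% when the mediators predict drinking but are not moved, and 2-4% when neither path exists. The correlations and shifts behind these figures are assumptions.

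Two stronger readings are tempting and not supported. One is that a false claim has a 30-50% chance, or even 71%, without qualification. The upper range needs a particular state of the world, and 71% ignores both the correlation and the need for two significant paths. The other is that 24 is a minimum, when 16 is possible and the 24 are only 12 distinct paths.

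**What to change.** Choose one of two wordings.

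- **Exploratory.** Move hypothesis 2 to the exploratory list, in line with its own analysis section, and report all indirect effects as estimates with intervals and no significance claims. This needs no choice of mediator, outcome or model.
- **One confirmatory effect.** Name a single indirect effect, tested at .05, and report the rest as exploratory estimates with intervals. One candidate is the combined effect through the three 1-month mediators on weekly consumption at 2 months, from the joint model. Weekly consumption is the outcome used for the power calculation. At 1 month the SMS and telephone routes still collect the mediator questions from nonresponders, whereas at 2 months they collect only the primary alcohol outcomes.

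Either takes about two sentences and no new data. The cost is that single-factor results lose confirmatory status. A combined effect also does not show by itself which factor mediates, and opposite effects could cancel within it, so the single-factor estimates should still be reported.

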**Figure 2 figure2:**
[figure not shown]
Advertisements shown in search and on Facebook.

The control group will be randomized further into 2 groups (Info-1 and Info-2). Both Info-1 and Info-2 will receive a single SMS message with basic health information regarding short- and long-term effects of alcohol consumption. In this substudy, we incorporate a contrast between 2 very brief types of information; one which emphasizes possible complexities associated with the short- and long-term effects of alcohol (such as is widely available from alcohol industry sources [49], Info-1) and another which provides a clear and straightforward public health messaging style (while being appropriately evidence informed, Info-2). Each is delivered in a single SMS and includes the same link to a Swedish website with information about alcohol and society (IQ). As individuals who have enrolled are looking for help to change their alcohol consumption, we anticipate that most participants will be motivated to click on the link. It is plausible that either type of message could encourage trial participants more than the other to click on the link. This exploratory substudy concerned with the direct behavioral effects on accessing health information will assist further consideration of the design of control conditions and be relevant to alcohol health promotion more broadly. As there is some health information provided, including to participants who do not click on the link, we refer to the control condition as alcohol information. Please see Multimedia Appendix 2 for more details.

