#### Follow-Up

At 1 month after randomization, an SMS message will be sent to both intervention and control with a hyperlink to a questionnaire exploring mediators. At 2 and 4 months after randomization, an SMS message will be sent to both intervention and control with a hyperlink to a questionnaire exploring alcohol consumption. At 2 months after randomization, the questionnaire exploring recall of trial procedures will be added for both groups. At 4 months after randomization, the intervention group will receive questions regarding the usability and their experiences of the intervention, and the control group will receive questions regarding their experiences of being allocated to the control condition.

Figures 3 and 4 offer an overview of the design in the form of a Standard Protocol Items: Recommendations for Interventional Trials figure and Consolidated Standards of Reporting Trials flowchart.

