**Exploratory Hypotheses**
6. Alcohol consumption will differ between groups Consent-1 and Consent-2 at 2 and 4 months after randomization. The 2-month interval will be primary.7. Alcohol consumption will differ between groups Info-1 and Info-2 at 2 and 4 months after randomization. The 2-month interval will be primary.

With regard to recall of trial procedures, there are 3 parameters that are of interest. First, participants will be asked if they recall receiving information about allocation to 2 different groups. As information regarding group allocation was presented identically for Consent-1 and Consent-2, this question will both work as a check that randomization succeeded and as a general baseline for recall regardless of group allocation. Second, participants will be asked if they recall how personal data will be handled in the study and their rights to these data. Finally, participants will be asked if they remember how the data would be analyzed and results communicated (see Multimedia Appendix 3).

We wish to measure if participants access further health-related information after reading a short SMS with basic information about short-term and long-term consequences of alcohol consumption. A proximal outcome of this is to measure whether or not participants in Info-1 and Info-2 request more information by following the included hyperlink. In addition, a short questionnaire at 4-month follow-up will investigate the control group participants, which will be used to investigate further differences between Info-1 and Info-2 (see Multimedia Appendix 3).

The acceptability and usability of the intervention will be measured through a questionnaire and the system usability scale [57] at 4-month follow-up (see Multimedia Appendix 3). The system usability scale comprises 10 Likert items exploring users’ perception on usability of a product or service.

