### Follow-Up Attempts

There are 3 follow-up stages: 1, 2, and 4 months after randomization. All follow-ups will be initiated by sending SMS messages to participants with hyperlinks to questionnaires. In all cases, the following attempts will be made to collect data from nonresponders:

A total of 2 reminders will be sent 2 days apart to those who have not responded.If no response is given to (1), then we will send questions directly in an SMS message, asking participants to respond directly with an SMS (no hyperlink).At 1 month, we will ask all 3 mediator questions.At 2 and 4 months, we will only ask for primary alcohol outcome measures.If there is no response given to (2), we will attempt to call participants to collect responses to the same questions as in (2). A maximum of 5 attempts will be made.

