Whether or not individuals requested more information by pressing the hyperlinks will be regressed against both group allocation (Info-1 and Info-2) and fixed responses to the control group experience questionnaire using logistic regression. Adjusted models will be explored that include baseline characteristics. Differences among the 2 groups on responses to the control group experience questionnaire will be investigated using chi-square tests or Fisher exact tests for comparison of proportions.

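### The only model stated for hypothesis 5 adjusts for 4-month questionnaire answers, so its allocation coefficient need not estimate the randomized Info-1 versus Info-2 contrast, and controls without answers are lost

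*Protocol article*

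**What the plan says.** All references are to the protocol article.

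- **Hypothesis.** The hypotheses textbox lists hypothesis 5 among the main hypotheses: "Rates of accessing further information will differ between groups Info-1 and Info-2".
- **Outcome.** Measures gives the primary outcome as "Rates of additional information being requested by pressing on the supplied hyperlink".
- **Exposure.** Intervention and Control Conditions says of the two messages: "Each is delivered in a single SMS and includes the same link to a Swedish website". Measures adds: "A proximal outcome of this is to measure whether or not participants in Info-1 and Info-2 request more information by following the included hyperlink".
- **Model.** Statistical Analysis Methods, Hypothesis 5, says that pressing the link "will be regressed against both group allocation (Info-1 and Info-2) and fixed responses to the control group experience questionnaire using logistic regression". Further adjusted models add baseline characteristics. The same section also compares the questionnaire answers between the two Info groups, which treats them as an outcome of the message.
- **Timing of the questionnaire.** Measures: "a short questionnaire at 4-month follow-up will investigate the control group participants". Follow-Up agrees, stating for 4 months after randomization that "the control group will receive questions regarding their experiences of being allocated to the control condition".
- **Fallback for non-responders.** Follow-Up Attempts limits the SMS step: "At 2 and 4 months, we will only ask for primary alcohol outcome measures". The phone step asks the same questions as the SMS step.
- **Population and missing data.** Statistical Analysis Methods promises that every randomized person is included, starts from complete cases, and offers multiple imputation as a sensitivity analysis for missing outcome data.

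**The concern.** Hypothesis 5 is a plain randomized comparison of two click rates. The stated model puts beside allocation a set of answers that were themselves given after allocation. With one SMS and a click described as proximal, those answers generally come after the outcome as well.

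If the answers are influenced by the message and also by having clicked, holding them fixed creates an association between message and click that randomization had removed, or distorts one that exists. A cause shared by clicking and answering, such as motivation, has the same effect. The article contemplates both links, since it tests the answers by Info group and relates them to the click in the regression.

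The second cost is the analysis set. Whether a control pressed the link can be known without any follow-up contact, but the model can be fitted only where the questionnaire was answered. That conflicts with the promise to include everyone randomized. People recovered by SMS or phone do not help, because those steps do not ask the experience questions.

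**Working it through.** **1. Plan figures.** The article gives no click rate, power or sample size for hypothesis 5. Its overall size does reproduce. 1800/0.85 = 2118, and averaging 1800/r − 1800 over the stated beta distribution for r gives a mean loss of 325 (interquartile range 231 to 398), against 326 (231 to 398) and N = 2126 in the article. With allocation probability 0.5, controls number 2126/2 = 1063. The Info split is not given in the text; assuming 1:1, each Info group has about 531.

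**2. Effect of conditioning on an answer.** Assume one binary questionnaire item whose odds are k·a^x·b^y. Here x is the Info group, y the click, a the odds ratio of the message on the item, b the odds ratio of the click on the item, and k the baseline odds. Within each level of the item,

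OR(x,y | item) = OR(x,y) × M, with M = (1 + ka)(1 + kb) / [(1 + k)(1 + kab)].

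M is the same at both levels of the item and does not depend on the click rate. None of a, b or k is in the documents, so all are assumptions.

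| Links | k | M |
|---|---|---|
| a = b = 1.5 | 1 | 6.25/6.5 = 0.96 |
| a = b = 2 | 1 | 9/10 = 0.90 |
| a = b = 2 | 1/2 | 4/4.5 = 0.89 |
| a = b = 3 | 1 | 16/20 = 0.80 |
| a = b = 3 | 1/3 | 4/5.33 = 0.75 |
| a = 2, b = 1/2 | 1 | 4.5/4 = 1.125 |
| a = 2, b = 1/2 | 1/4 | 1.6875/1.5625 = 1.08 |
| a = 3, b = 1/3 | 1 | 5.33/4 = 1.33 |
| a or b equal to 1 | any | 1.00 |

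For a = b, k = 1/a gives the largest shift; for very rare or very common answers M moves back towards 1. A true odds ratio of 1.50 with k = 1 becomes 1.5 × 0.90 = 1.35 (both links OR 2) or 1.5 × 0.80 = 1.20 (both OR 3).

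**3. Cross-check by simulation.** This used a five-level item, a 50% click rate and equal shifts from message and click of 0.2, 0.5 and 0.8 SD. A true odds ratio of 1.00 became 0.96, 0.80 and 0.56. At n = 904 the false-positive rate was 5.9%, 38% and 98%, against about 5% for the allocation-only model. With only one link the odds ratio did not move.

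**4. Analysis set.** At the assumed 85% response at 4 months, 1063 × 0.85 = 904 controls remain and 159 are dropped. The standard error grows by 1/√0.85 = 1.085, about 8%. For a difference in click rates near 50%, it goes from √(0.5/531.5) = 0.031 to √(0.5/(531.5 × 0.85)) = 0.033. This is a minimum: the 85% counts people reached by SMS and phone, who have no questionnaire answers. How many fewer remain cannot be derived from the article.

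**The case against.** - **Bias is conditional.** This stands. With only one link the odds ratio stays at 1.00, and with both at OR 1.5 it moves only to 0.96. The questionnaire items are in an appendix not shown, and the documents give no basis for saying that the wording of one SMS shifts answers by OR 2 to 3 four months later. A reader might infer that the estimate is known to be biased; the documents do not support that. What they do show is a model that does not in general target the stated contrast, while the allocation-only model does so whichever links exist.
- **Two regressions may be meant.** The sentence could describe one regression on allocation and another on the answers, and the hypothesis 3 analysis does first regress its outcome on allocation alone. This is the less natural reading of a single sentence joining the two sets of regressors. If it is intended, the text should say so.
- **No click window is given.** Correct, so the order of click and answer is inferred from the single SMS and the proximal outcome. A click after the questionnaire would not rescue the model: the answer is still post-randomization and could then lie on the path from message to click.
- **Imputation is planned.** It is a sensitivity analysis for missing outcome data, so it does not clearly cover a missing regressor.
- **The loss could be far larger.** A reader might suppose that only half the controls answer the web form, which would raise the standard error from 0.031 to 0.043 (41%). That response figure is hypothetical; only 85% is documented.
- **The substudy is exploratory.** Intervention and Control Conditions and Limitations both say so, and Limitations adds that the substudies are unpowered. This lowers the severity but does not make the model right for its hypothesis.
- **An analysis plan may settle it.** The point concerns a model that the article states, not a detail it leaves out.

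**Conclusion.** The point holds, at moderate severity. As written, the only hypothesis 5 model conditions on answers given after randomization and generally after the click, so its allocation coefficient does not in general estimate the randomized Info-1 versus Info-2 contrast.

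The size of any bias depends on unknown links. A null odds ratio could remain at 1.00, fall to 0.75 with both links at OR 3 in the same direction, or rise to 1.33 with such links in opposite directions. These figures illustrate what could happen and do not predict the result. The loss of controls is firmer: at least about 159 of 1063 at the documented 85%, under the complete-case default and against the plan's own promise to analyse everyone randomized.

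Because hypothesis 5 is listed as a main hypothesis, a reader might infer that the trial's principal conclusion is at risk. It is not. The comparison of intervention with control on alcohol consumption does not use this model.

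**What to change.** Replace the model sentence under Hypothesis 5 with these provisions:

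- The test of hypothesis 5 is a logistic regression of the click (yes/no) on Info-1 versus Info-2 in all control participants as randomized.
- The adjusted version adds baseline characteristics only.
- The planned comparison of questionnaire answers between the Info groups stays as it is.
- Any association between clicking and later answers is reported separately, as descriptive, among those who answered.

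The cost is one revised sentence and, if the association is still wanted, one extra descriptive table. No new data are needed. If two separate regressions were always intended, the same sentence makes that clear.
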